### Secondary study outcomes

#### Complications

Access-related complications requiring pharmacological, surgical or endovascular interventions will be registered from randomisation until the end of the study period or death. Furthermore, the number of days admitted to hospital or visiting outpatient clinics for any reason and for vascular access-related reasons per person-year will be registered. Finally, all-cause mortality from randomisation to the end of the study period will be registered.

#### Patient-reported outcome measures

Short-Form Health Survey (SF-12) and the Dialysis Symptom Index (DSI) measure generic health-related quality of life as well as disease-specific symptom burden.^26^
^27^
The Short-Form Vascular Access Questionnaire (SF-VAQ) measures haemodialysis patients’ satisfaction with their vascular access.^28^
The 5-Level EuroQol 5-Dimensional Questionnaire (EQ-5D-5L) measures health-state utility values.^29^

The SF-VAQ will be administered on a monthly basis, whereas the SF-12, DSI and EQ-5D-5L will be administered at 3-month intervals. To lower their burden, participants who have started haemodialysis treatment will receive the questionnaires during these treatments and will get assistance from a nurse. The questionnaires will be administered from randomisation until the 1 year after study or dialysis initiation, whichever is later.

Other outcome measures will be registered for exploratory analyses and are defined according to the ESVS guidelines on vascular access^5^:

Primary, assisted primary, secondary and functional patency of vascular access.Time until vascular access maturation (definition according to the American Society of Nephrology).^30^
Time until functional vascular access.The number of haemodialysis sessions with inadequate haemodialysis dose (Kt/V) and with cannulation difficulties or failure. Cannulation difficulties or failures will be recorded with the use of monthly questionnaires asking dialysis nurses whether more than one cannulation attempt was required, whether two-needle cannulation was impossible or if cannulation was painful.

### Quality and safety

Data are entered on electronic case report forms by trained investigators using numerical codes that cannot be traced to the individual subjects. The subject identification code list is kept by the principal investigator at each study site. Any serious adverse events that may occur will be reported to the principal investigator without undue delay after obtaining knowledge of the events. To evaluate differences in serious adverse events and mortality between treatment arms, an interim safety analysis will be performed and presented to a data safety monitoring board every 6 months. Significant differences on safety outcomes may lead to discontinuation of the trial. Furthermore, an independent monitor will be appointed to assess trial processes and data.

### Sample size calculation

Sample size was estimated for the primary study outcome of access-related intervention rates. Since two intervention groups will be compared with the usual care group, we used Bonferroni correction to account for multiple comparisons, which resulted in an alpha of 0.025. The average number of interventions per year for patients receiving an autologous arteriovenous fistula has previously been reported at 2.48 interventions per year.^31^ The clinically relevant effect size was considered to be one percutaneous intervention per year and 0.5 surgical interventions per year. Since these interventions occur at a ratio of 1.0:0.7,^31^ a reduction of the overall intervention rate by 0.80 interventions per year was used as the clinically relevant effect for sample size calculations.

With these assumptions, a total number of 195 patients (65 patients in each treatment arm) with 1 year of follow-up achieves 80% power to detect a 0.80 decrease in the number of access-related interventions per person-year of haemodialysis treatment between the intervention groups and the usual care group using a two-sided, large-sample z-test of the Poisson event–rate difference at a significance level of 0.025.^32^

Since the study includes patients with a limited life expectancy, a substantial proportion of participants are expected to die before contributing 1 year of follow-up. To compensate for the resulting loss of statistical power, the trial has a variable follow-up with trial closeout for all patients at the time when the last patient enrolled has 1 year of follow-up. Since participant recruitment is expected to take 2 years, the resulting additional follow-up time will more than compensate for the loss of follow-up due to patient mortality in the first year of the study period.

### Data analysis plan

The access-related intervention rates will be analysed using a general linear model with Poisson distribution and identity link, and with time as off-set variable. Both intervention (ie, the prosthetic arteriovenous graft and central venous catheter) groups will be compared with the usual care (autologous arteriovenous fistula) group. Non-adherence to the allocated treatment group is expected as patients cross over to another surgical strategy for vascular access when the randomised strategy is no longer feasible. The primary analysis will be on the intention-to-treat population. Exploratory on-treatment analyses will be performed as well. A subgroup analysis will be performed for patients who had already started haemodialysis using a catheter before inclusion.

Formal statistical comparisons will be made for the following secondary study outcomes:

SF-12/DSI and SF-VAQ summary scores using generalised estimating equations.The number of access-related serious adverse events per person-year using general linear models with Poisson distribution and mortality using Cox regression.The number of days admitted to the hospital or visiting outpatient clinics for any reason per person-year using Student’s t-tests.

Primary outcome data are not expected to be missing, as interventions on vascular access will be reported in the patients’ medical files. We expect little to no loss to follow-up since study participants will be observed three times per week in the dialysis unit and the trial requires no additional study visits. PROMs will be analysed using generalised estimating equations that allow for missing data. Other missing data will be handled by using 10 imputation cycles with regression methods, performing standard analyses for each imputation cycle and considering the variability across the imputation cycles in the final analysis.

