### External validation of a mortality prediction model

Elderly haemodialysis patients form a heterogeneous population in terms of comorbidities and life expectancy. The majority of elderly haemodialysis patients have multiple comorbidities and a relatively short life expectancy, making the long-term performance of the vascular access less relevant. However, for the small group of elderly patients with an unusually long life expectancy, autologous arteriovenous fistulas are considered to be the best vascular access, given their low complication rates after maturation. To identify this subset of elderly patients that should be excluded from randomisation, we performed an external validation of the mortality prediction score developed by Dusseux *et al*.^17^ This prediction score contains items readily identified from the medical history and can be completed before initiation of haemodialysis treatment.

The mortality prediction score was validated in the Netherlands Cooperative Study on the Adequacy of Dialysis (NECOSAD).^18 19^ In this multicentre observational cohort study, adult patients starting dialysis treatment between 1997 and 2007 in the Netherlands were prospectively followed up until 1 February 2015. For the current validation, we restricted the sample to haemodialysis patients aged 70 years and older. This resulted in 494 patients, 411 of whom died during follow-up with a median survival of 2.3 years (IQR 1.1–4.4 years). Overall, baseline characteristics in the validation cohort were comparable to those in the Dusseux cohort (table 1).^17^ Missing data were assumed to be largely missing at random. Therefore, 10-fold multiple imputation with fully conditional specification was performed using the R package ‘mice’. All variables of the mortality prediction score and the outcome were included in the imputation model.^20 21^

**Table 1 T1:** Baseline characteristics of the NECOSAD validation cohort compared with the Dusseux derivation cohort^17^

	NECOSAD cohort n=494	Dusseux cohort n=8955
Gender (male) (%)	61	60
Age (years)	76 (73–79)	78 (74–82)
Diabetes (%)	25	38
Ischaemic heart disease (%)*	31	14
Peripheral vascular disease (%)	24	27
Cerebrovascular disease (%)	14	12
Congestive heart failure (%)	19	34
Dysrhythmia (%)†	22	25
Respiratory disease (%)‡	12	13
Active malignancy (%)	4	11
Psychiatric disorder (%)§	3	4
Mobility (%)¶**		
Walks without help	64	69
Needs assistance for transfers	32	22
Totally dependent for transfers	4	9

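### The primary analysis and the sample size both assume Poisson variance, with no allowance for between-patient differences in intervention rate, so the stated error rate and power are conditional on that assumption

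*Protocol article*

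**What the plan says.** The Data analysis plan fixes the primary model: "The access-related intervention rates will be analysed using a general linear model with Poisson distribution", with an identity link and time as an offset. The same family is used for a secondary outcome: "The number of access-related serious adverse events per person-year using general linear models with Poisson distribution".

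The Sample size calculation makes the same assumption. It works "using a two-sided, large-sample z-test of the Poisson event–rate difference at a significance level of 0.025" and concludes that 65 patients per arm with one year of follow-up "achieves 80% power to detect a 0.80 decrease in the number of access-related interventions per person-year of haemodialysis treatment". On multiplicity, "we used Bonferroni correction to account for multiple comparisons, which resulted in an alpha of 0.025".

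Neither section mentions a dispersion parameter, a negative binomial or quasi-Poisson model, a patient effect or a robust variance. The only allowance beyond the basic calculation is the variable follow-up, and the article gives its purpose as offsetting early deaths. The section on the mortality prediction model says: "Elderly haemodialysis patients form a heterogeneous population in terms of comorbidities and life expectancy".

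**The concern.** Access interventions are recurrent events, and patients are unlikely to share one underlying rate. The article describes several sources of difference: fistulas that never mature, a mix of predialysis patients and patients already dialysing through a catheter, some catheter-arm patients who need no new insertion, and interventions before dialysis that are counted while only haemodialysis years enter the denominator.

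If rates differ between patients, the variance of a count exceeds its mean. A Poisson standard error is then too small, the Bonferroni level of 2.5% per comparison is not held, and a test that does hold it has less power than the sample size section states. The superiority claims for grafts and catheters rest on this test.

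**Working it through.** **Inputs from the Sample size calculation.** The fistula rate "has previously been reported at 2.48 interventions per year"; "a reduction of the overall intervention rate by 0.80 interventions per year was used as the clinically relevant effect for sample size calculations". So λ0 = 2.48 and λ1 = 1.68. Two-sided α = 0.025 gives z = 2.2414; 80% power gives z = 0.8416. There are 65 patients per arm with 1 year each.

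**Step 1: reproduce the stated figure.** With variance equal to the mean:

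n = (2.2414 + 0.8416)² × (2.48 + 1.68) / 0.80² = 9.505 × 4.16 / 0.64 = 61.8 per arm.

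Power at 65 = Φ(0.80 / √(4.16/65) − 2.2414) = Φ(3.162 − 2.241) = 82.1%.

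With the unrounded effect, (1.0 × 1 + 0.7 × 0.5)/1.7 = 0.794, n is 62.8 and power at 65 is 81.5%. The arithmetic is sound, under Poisson variance.

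**Step 2: add heterogeneity on the stated 1-year basis.** The documents give no dispersion figure. Assume patient rates vary by a gamma factor with mean 1 and variance φ, so Var = μ + φμ².

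- Error of the Poisson test = 2 × [1 − Φ(2.2414 / √(1 + 2.48φ))]. At φ = 0.5: 2.2414/√2.24 = 1.498, which gives 13.4%.
- Variance sum for power = 4.16 + φ(2.48² + 1.68²) = 4.16 + 8.973φ. At φ = 0.5 this is 8.646; power with the correct variance = Φ(0.80/√(8.646/65) − 2.2414) = Φ(−0.048) = 48%.
- Valid power falls below 80% once φ exceeds (65 × 0.64/9.505 − 4.16)/8.973 ≈ 0.024.

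**Step 3: planned variable follow-up.** Assume uniform 2-year accrual, closeout one year after the last enrolment and exponential survival with median 2.2 years (the figure in the Ethics section). All follow-up is treated as haemodialysis time. Mean follow-up is then about 1.455 years and E[t²]/E[t] is about 1.871. The Poisson test's variance is now understated by a factor of 1 + φ × 2.48 × 1.871. At φ = 0.5 that is 3.32, and 2.2414/√3.32 = 1.230 gives an error of about 22%. Simulation (20,000 trials per setting) agrees. Valid power stays at 80% up to φ of about 0.13: (4.3767 − 4.16/1.455) / (8.973 × 1.871/1.455) ≈ 0.13, where 4.3767 = 65 × 0.64/9.505.

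**Step 4: index access creation as a fixed event.** The Primary study outcome section counts procedures from randomisation, so access creation is itself a counted event and is close to certain for most patients. Give each patient exactly one such event and apply the gamma factor only to later interventions, with the overall rates unchanged (residual rates 2.48 − 1/1.455 = 1.79 and 1.68 − 1/1.455 = 0.99).

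Approximate results, in %. Error is per comparison for the Poisson test (nominal 2.5); power is with a valid or robust variance. The second block of columns is Step 3 and the last is Step 4.

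| φ (assumed) | 1 year: error | 1 year: power | Variable: error | Variable: familywise error | Variable: power | Fixed index event, variable: error | Fixed index event, variable: power |
|---|---|---|---|---|---|---|---|
| 0 | 2.5 | 82 | 2.5 | 5 | 94 | 1 | over 96 |
| 0.1 | 4.5 | 73 | 6 | 12 | 84 | 3 | 96 |
| 0.25 | 8 | 62 | 13 | 22 | 69 | 5–6 | 90 |
| 0.5 | 13 | 48 | 22 | 36 | 50 | 11 | 78 |
| 1.0 | 23 | 32 | 35 | 53 | 30 | 21 | 56 |

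With the fixed index event and exactly 1 year each, error at φ = 0.25 / 0.5 / 1.0 is 1.4 / 2.6 / 6.6% and robust power 96 / 90 / 79%.

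In every scenario a patient-level robust standard error kept the error per comparison at about 2.3 to 3.0%.

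**The case against.** The strongest reply is that the article names a distribution, link and offset but not how standard errors are computed. A Poisson mean model with sandwich errors is compatible with its wording, and such detail may be in an analysis plan that is not shown. That is fair for the analysis half and lowers the severity. It does not help the sample size, which names the Poisson z-test and so fixes variance equal to the mean. As written, the analysis matches that assumption.

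Second, the support for heterogeneity is indirect. The sentence on a heterogeneous population concerns comorbidity and life expectancy, not intervention rates, and the article does not say that a failed fistula brings repeated procedures. This stands: φ is an assumption, and φ = 0 has to be part of the range.

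Third, the near-certain index procedure reduces variance. This also stands. It roughly halves the inflation under variable follow-up and makes the Poisson test conservative at low φ. It rests on 2.48 including the index procedure, which the article does not settle. Against it, dividing predialysis interventions by haemodialysis years alone could add dispersion.

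A reader might go further and infer that the 5% familywise level is lost and that power is well under 80%. The documents do not support that as fact, because both depend on an unknown φ. Under the planned follow-up, valid power is still 84% at φ = 0.1. A reader might also infer that longer follow-up fails to compensate for deaths. That is not shown: variable follow-up against exactly 1 year gives valid power of 94 v 82% at φ = 0, 69 v 62% at 0.25, 50 v 48% at 0.5 and 30 v 32% at 1.0.

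**Conclusion.** The point holds in conditional form. The primary analysis and the sample size share one unstated condition, that each patient's count has variance equal to its mean, and nothing in the article allows for departure from it. The 80% power is correct under that condition. Under the planned follow-up it survives only to φ of about 0.13 if the whole rate varies between patients; with a fixed index event it is still about 90% at φ = 0.25 and slips just below 80% (78%) at 0.5.

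The Poisson standard error can be wrong in either direction. Inflation is the more likely under variable follow-up, because the variance from patient differences grows with the square of observation time. How large it is cannot be settled from the documents; the figures are illustrative and rest on the gamma form, the accrual and survival assumptions, and all follow-up being haemodialysis time.

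This should be fixed but does not invalidate the design: the rate estimate is unaffected and the remedy is a choice of standard error.

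**What to change.** Keep the rate model and the sample size. Specify patient-level robust (sandwich) or bootstrap standard errors for the primary intervention rate and for the access-related serious adverse event rate. Put this in writing before the treatment code is unlocked, so that the variance method cannot be seen as chosen on the results.

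Restate the 80% power as conditional on Poisson variance, and give a range over dispersion that starts at 0, with the treatment of the index procedure made explicit.

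The cost is a few sentences in the analysis plan, possibly wider confidence intervals and a less favourable stated power. If the counts prove to be Poisson, almost nothing is lost: at φ = 0 on the 1-year basis the robust test has 82% power, as does the Poisson test.

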### Primary study outcome

The primary study outcome is the number of access-related interventions required for each person-year of haemodialysis treatment. To analyse this, we will divide the total number of interventions during follow-up by the total number of haemodialysis years. The primary outcome corresponds to the proposed core outcome measure for haemodialysis vascular access.^25^ This outcome measure includes all percutaneous access interventions, surgical access procedures and catheter interventions from randomisation until the end of the study period or death. The outcome measure specifically includes interventions before dialysis initiation and after dialysis cessation in the occasional patient who stops haemodialysis treatment after kidney transplantation, peritoneal dialysis, recovery of renal function or refusal of further haemodialysis. These vascular access interventions before dialysis initiation and after dialysis cessation are included as they are part of the standard care that this trial evaluates. Patients who discontinue haemodialysis treatment will therefore remain in the trial. Access-related complications that are resolved using conservative or pharmacological treatment are not counted as interventions.

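### The primary Poisson model enters time as an offset under an identity link, so its arm coefficient is a difference in counts and not the intervention-rate difference the trial is powered on

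*Protocol article*

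**What the plan says.** The Data analysis plan states that intervention rates will be analysed with a "general linear model with Poisson distribution and identity link, and with time as off-set variable", comparing the graft and catheter arms with the fistula arm. Three other statements in the protocol article define what this model has to estimate:

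- Primary study outcome: "The primary study outcome is the number of access-related interventions required for each person-year of haemodialysis treatment". The estimator is also given: "we will divide the total number of interventions during follow-up by the total number of haemodialysis years".
- Sample size calculation: the test is a "two-sided, large-sample z-test of the Poisson event–rate difference at a significance level of 0.025", with 65 patients per arm and a target reduction of 0.80 per person-year from 2.48.
- Sample size calculation, on follow-up: "the trial has a variable follow-up with trial closeout for all patients", at the point when the last patient enrolled has one year. Recruitment is expected to take 2 years, and many participants are expected to die within their first year.

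**The concern.** An offset is a known term in the linear predictor whose coefficient is fixed at 1. Under a log link, log(time) as offset makes the mean equal to time × rate, which is why offsets are routine for rates. Under an identity link the same device gives a mean of time + b0 + b1·arm. Three things follow.

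- The arm coefficient is in interventions per patient, not interventions per year, so it cannot be read against the 0.80 target.
- The slope of the count on time is held at 1 per year in every arm, although the protocol expects 2.48 and 1.68. The variation with time that this leaves out is not reflected in the model-based standard error.
- If one arm has less time because more patients die, its counts fall and the model reports part of that as a treatment effect. The arm with shorter survival looks better. The Introduction and the Ethics section both acknowledge a reported association of catheters with mortality, although the Ethics section disputes that it is causal.

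This is the only primary analysis stated.

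**Working it through.** **Inputs.** From the Sample size calculation: fistula rate 2.48 per year, reduction 0.80 (so 1.68), 65 per arm, two-sided alpha 0.025 per comparison, 80% power, 2 years' recruitment, closeout one year after the last enrolment (potential follow-up about 1 to 3 years). From the Ethics section: median survival 2.2 years. Assumed here: uniform accrual, exponential survival, pure Poisson counts, and follow-up from randomisation as the time variable.

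**The protocol's own sample size.** For a difference in Poisson rates over one year:

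`n per arm = (z[1-alpha/2] + z[power])² × (λ0 + λ1) / (λ0 - λ1)²`

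`= (2.241 + 0.842)² × (2.48 + 1.68) / 0.80² = 61.8`, so 62 per arm.

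With the unrounded effect `(1.0×1 + 0.7×0.5)/1.7 = 0.794` it is 62.8, so 63. The stated 65 is slightly conservative (power 82.1% at 0.80). The design therefore rests on a rate difference.

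**What the written model estimates.** The model is `E[Y] = t + b0 + b1·arm`. If everyone has the same time T, the true means are `λ0·T` and `λ1·T`, so

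`b1 = (λ1·T - T) - (λ0·T - T) = T × (λ1 - λ0)`

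| T (years) | b1 | True rate difference |
|---|---|---|
| 1 | -0.80 | -0.80 |
| 1.5 | -1.20 | -0.80 |
| 2 | -1.60 | -0.80 |

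The two agree only at T = 1.

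**Variable follow-up, large sample (200,000 per arm).** Mean time is 1.45 years. The written model gives b1 = -1.10. A model with mean `t × (b0 + b1·arm)` gives -0.80 on the same data.

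**Trials of the planned size (65 per arm).** The runs, each of at least 1,000 simulated trials, differ slightly by simulation error, so ranges are given.

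| Scenario | Model as written | Total events / total time |
|---|---|---|
| 2.48 vs 1.68 | mean b1 -1.09 to -1.11; mean SE 0.28, actual SD 0.34 to 0.36 | about -0.80; SE 0.21, SD 0.21 |
| 2.48 in both arms, same survival | rejects 7.8% to 9.3% at nominal 2.5% | rejects 2% to 3% |
| 2.48 in both arms, 1.5-fold mortality in one (assumed) | mean b1 -0.31 to -0.33; rejects 17.5% to 21% | about 0.00; rejects about 2.7% |

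**Rough check of the last row.** The extra mortality shortens mean time by about 0.19 year. The model allows for only 1 of the 2.48 interventions per year, so about `(2.48 - 1) × 0.19 = 0.28` interventions are left for b1 to absorb. This is close to the simulated value. With median survival of 2.2 against 1.7 years (also assumed), the spurious coefficient is -0.20.

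**The case against.** The strongest reply is that the intended analysis is clear from the rest of the article. The outcome section divides events by haemodialysis years, the power calculation uses a rate difference, and the model sentence itself speaks of rates. With arm as the only factor, an identity-link Poisson model in which time multiplies the rate has exactly the ratio of totals as its maximum-likelihood estimate. On that reading, offset is loose wording for exposure and the analysis is sound.

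That is probably what the authors meant, and it is why the correction is cheap. It does not rescue the sentence. The article names both the link and the offset, so this is not a detail left to an analysis plan. In the simulations, software given that specification fitted the additive model without error or warning, so the mistake could pass unnoticed.

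Some limits on the size do stand:

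- The model fixes only the slope on time at 1. The intercept is free, so fitted means are not themselves 1 per year.
- The mortality effect depends on the gap assumed: about -0.06 for a hazard ratio of 1.1, -0.18 for about 1.3 and -0.32 for 1.5. The documents predict no such gap.
- In the powered scenario the written model still rejects 91% of the time, against 94% for the rate analysis. The harm there is to the estimate and its standard error more than to detection.
- The simulated time is follow-up from randomisation. Haemodialysis years will be distributed differently, because patients may be enrolled up to 6 months before dialysis is expected to start.

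**Conclusion.** The primary model is wrong as written and must be corrected before analysis. That b1 is a count difference follows from algebra and needs no assumption, and the planned variable follow-up means it will not coincide with the rate difference. Under the accrual and survival assumptions above, the estimate is about -1.10 instead of -0.80, the standard error is about a fifth too small (0.28 against about 0.35), and the type I error is roughly three times nominal. Bias from unequal survival is certain in direction for rates above 1 per year, but its size depends on a mortality difference that can only be assumed. Neither the outcome definition nor the sample size is at fault.

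**What to change.** Replace the model sentence. The smallest change, which keeps the identity link and matches the powered rate difference, is:

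> Intervention counts will be analysed with a generalised linear model with Poisson distribution and identity link, with mean equal to exposure × (b0 + b1·graft + b2·catheter), without a separate intercept and without an offset; b1 and b2 are the rate differences per person-year.

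An equally valid alternative is a log link with log(exposure) as offset, reporting the rate difference by marginal standardisation with its confidence interval. With arm as the only factor, both reproduce the ratio of totals in the outcome definition.

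The sentence should also name the exposure as haemodialysis years and say how patients with interventions but no haemodialysis time are handled. The outcome definition counts their interventions, but neither model can be fitted to a positive count at zero exposure.

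The cost is one sentence in the protocol and analysis plan. Data collection and sample size do not change.

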We performed a comprehensive search in international trial registers for ongoing and planned randomised trials on vascular access creation in elderly haemodialysis patients. Four ongoing trials were identified that allocate participants to arteriovenous fistula or graft surgery. One trial has a single-centre design and plans to enrol 270 haemodialysis patients aged 70 years or older. The participants are followed up for 2 years after vascular access creation for the primary outcomes, which are vascular access use as well as patency.^12^ The remaining three trials are pilot studies evaluating the feasibility of the trial design. These pilot studies allocate patients aged 65 years or older, either at the time of referral for vascular access, at dialysis initiation or after dialysis initiation with a catheter.^13–15^ We also identified two trials allocating participants to fistula creation or catheter insertion. The ACCESS HD feasibility study allocates patients aged 55 years or older who have already commenced haemodialysis treatment with a catheter to either fistula creation or continued catheter use.^11^ The AUSTrian Randomized Interventional Study on Dialysis Accesses (AUSTRIA) aims to allocate 220 participants aged 60 years or older to one of the two treatment arms, with access-related complications being the primary outcome measure.^16^ Although these ongoing studies will surely provide valuable information, none of the trials cover the full spectrum of vascular access strategies in elderly haemodialysis patients.

The aim of the Optimising Access Surgery in Senior Haemodialysis Patients (OASIS) trial is to determine the best vascular access strategy for elderly haemodialysis patients. We hypothesise that arteriovenous grafts and central venous catheters are superior to autologous arteriovenous fistula for elderly patients starting haemodialysis treatment and result in reduced access-related intervention rates, greater patient satisfaction and lower healthcare costs.

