## Methods and analysis

### Study design

OASIS is a parallel group, multicentre, randomised controlled trial with a superiority framework and a 1:1:1 individual participant treatment allocation ratio over three study arms. Given the nature of the interventions, blinding healthcare providers, participants or outcome assessors for treatment assignment are not possible. However, data analysis will be performed without knowledge of treatment assignment by coding the treatment arms and unlocking the code only after statistical analysis is completed. Some 17 hospitals, together treating approximately 50% of all haemodialysis patients in the Netherlands, are expected to participate.

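### The aim is to find the best of three strategies, but the primary analysis prespecifies no graft-versus-catheter inference; a gated stepwise rule would add one and lose no rejection that Bonferroni makes

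*Protocol article*

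**What the plan says.** The Introduction states that the aim "is to determine the best vascular access strategy for elderly haemodialysis patients". The hypothesis that follows is narrower: "We hypothesise that arteriovenous grafts and central venous catheters are superior to autologous arteriovenous fistula". It is silent on graft against catheter. Study design describes a "superiority framework and a 1:1:1 individual participant treatment allocation ratio over three study arms".

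The Sample size calculation counts two comparisons with usual care: "we used Bonferroni correction to account for multiple comparisons, which resulted in an alpha of 0.025". The fistula rate "has previously been reported at 2.48 interventions per year", and "a reduction of the overall intervention rate by 0.80 interventions per year was used as the clinically relevant effect". The result is 65 patients per arm with 1 year each for 80% power.

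For the primary outcome, the Data analysis plan says that the graft and catheter "groups will be compared with the usual care (autologous arteriovenous fistula) group". It names no graft-versus-catheter contrast and describes no stepwise or closed procedure.

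**The concern.** The aim asks for a ranking of three strategies, while the primary analysis asks two questions that both refer back to fistula. If both answers favour the intervention, the trial shows that fistula is not best and stops there. Any graft-versus-catheter statement on intervention rates would then be an unplanned contrast, in the very scenario the investigators expect.

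The second part concerns efficiency. With exactly three arms, if any two of the three pairwise null hypotheses are true, the third is true as well. The only joint null that needs protection is therefore equality of all three arms. Once that is rejected, at most one pairwise null can still be true, and each pair can be tested at 0.05. Plain Bonferroni leaves this unused.

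**Working it through.** **Inputs.** From the Sample size calculation: fistula rate 2.48 per year; reduction 0.80, so 1.68 in an intervention arm; 65 patients per arm with 1 year each, so 65 person-years; two-sided alpha 0.05/2 = 0.025; Poisson variance.

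**The plan's own figure.** n = (z₀.₉₈₇₅ + z₀.₈₀)² × (λ₁ + λ₂)/d² = (2.241 + 0.842)² × (2.48 + 1.68)/0.80² = 9.505 × 6.5 = 61.8, so 62 per arm. With a continuity correction, (n/4) × [1 + √(1 + 4/(n·d))]² = 64.3, so 65 per arm. The stated size is reproduced. Uncorrected power at 65 per arm: standard error √(4.16/65) = 0.253; 0.80/0.253 = 3.162; Φ(3.162 − 2.241) = 82.1%.

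**Why the gated rule is valid.** The gate is that at least one fistula contrast has p < 0.025.
- All three rates equal: any false claim requires passing the gate, which has probability at most 2 × 0.025 = 0.05.
- Exactly one pair equal: only that null can be falsely rejected, and it is tested at 0.05 or less.
- No pair equal: no false rejection is possible.

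A contrast with p < 0.025 opens the gate by itself and also passes 0.05, so every Bonferroni rejection is kept.

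**Simulation.** 1,000,000 trials per scenario, Poisson counts on 65 person-years per arm, unpooled z-tests.

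Rates 2.48 (fistula), 1.68 (graft), 1.68 (catheter):

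| | Bonferroni | Gated rule |
|---|---|---|
| Power per fistula contrast | 82.4% | 86.7% |
| Power for both | 72% | 81% |
| Power for at least one | 92.7% | 92.7% |
| False graft-catheter rejection | not tested | 5.0% |

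With all rates equal at 2.48, the familywise error of the gated rule is about 4.6%. If only graft works (2.48, 1.68, 2.48), the true fistula-catheter null is rejected in about 4.3% of trials, and graft versus catheter is detected in about 77%.

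**Power for graft versus catheter.** The documents give no expected gap, so the catheter rates below are assumptions, with graft at 1.68. Power ≈ Φ(d/√((λ₁ + λ₂)/65) − 1.960).

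| Catheter rate | d / standard error | Power |
|---|---|---|
| 1.48 | 0.20/0.220 = 0.91 | about 15% |
| 1.28 | 0.40/0.213 = 1.87 | about 47% |
| 1.18 | 0.50/0.210 = 2.38 | about 66–67% |

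With fistula at 2.48 the gate costs almost nothing in these cases. It does cost power if fistula lies between the other two: at graft 1.68, fistula 2.08 and catheter 2.48, graft-catheter power falls from 89% ungated to 48% gated.

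**The case against.** The strongest reply is that the plan is coherent as it stands. The hypothesis concerns superiority over fistula only, two interventions against one control is a standard design, and alpha is split over exactly the comparisons made. The protocol promises 80% power per comparison and delivers it. It does not define success as winning both, so the gain from 72% to 81% is on a criterion the investigators did not set. All of this stands, and a reader who infers a faulty error rate or an underpowered trial goes further than the document supports.

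A reader might also infer that graft and catheter are compared nowhere. That is too strong. The Economic analysis section compares all the strategies, the Quality and safety section reviews events across arms, and the secondary comparisons are not restricted to fistula. The primary model holds all three arms, so the difference can be estimated. What is absent is a prespecified primary-outcome inference.

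A third reply is that Bonferroni appears only in the sample size section, and a stepwise procedure could sit in an analysis plan that is not shown. That is possible. But the article itself states both the comparisons and the correction, so the mismatch with the aim is in the text as it reads.

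Finally, adding the test will not reliably identify a best arm. That also stands: the trial is not sized for it, and if graft and catheter are truly equal there is nothing to find.

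**Conclusion.** The point holds as a gap between aim and primary analysis, together with an avoidable but modest loss of power. It is a worthwhile improvement and not a correction of an error. The gain is 4 to 5 percentage points per fistula contrast and about 9 points for showing both, with nothing gained for showing at least one. Graft versus catheter is added with no extra patients and without taking alpha from the planned contrasts.

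The power figures assume the plan's rates, Poisson variance and 65 person-years per arm; overdispersion would lower them all. The validity argument does not depend on those rates, provided that the tests use a valid variance. The graft-catheter power figures rest on assumed gaps.

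**What to change.** Add graft versus catheter to the listed primary-outcome comparisons, and state the rule before the treatment codes are unlocked: if either fistula contrast has p < 0.025, the other fistula contrast and graft versus catheter are each tested at two-sided 0.05; otherwise no confirmatory claim is made. Report the graft-catheter rate difference with its confidence interval whatever the gate decides, and say that the trial was not sized for this contrast and that the gate lowers its power when fistula lies in the middle.

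The cost is wording, plus one real drawback: no simple intervals match the stepwise decisions. An unadjusted 95% interval for a fistula contrast can exclude zero although the gate stays closed. This happens in 3% to 4% of trials in the plan's scenario and in about 16% with fistula midway (1.68, 2.08, 2.48). So keep 97.5% intervals for the fistula contrasts at the gate, and label any unadjusted 95% intervals as descriptive.
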